### Data collection

#### ADHD symptoms assessment

In the assessment of ADHD symptoms, Conners’ behavior rating scale which is a clinical tool evaluating child behavioral disorders will be used. Conners’ rating scale is divided into three categories, which are determined by the person who filled it (parent, teacher and self-report). For this trial, Conners’ parent rating scale (CPRS) [51] will be used. CPRS checklist makes parental reports of the children’s basic problems in the setting of outpatient psychiatry. The CPRS includes questions about different aspect of patients’ problems and shows different type of ADHD symptoms [51]. Conners’ questions gives ADHD Conners scores that indicates the severity of ADHD symptoms. In addition, all questions can be divided into three subscales by symptoms including inattention, hyperactivity/impulsivity, and combination type.

#### Electroencephalography

Electroencephalography (EEG) will be performed for 10 min using Brain Master Discovery from 19 scalp sites both before the first intervention and the 10 sessions of the therapy. The artifact-free periods of 1-min EEG data will be analyzed for quantitative EEG (QEEG) measures using the Neuroguide software. Background rhythm in relative power of theta (4–7.5 Hz), alpha (8–12 Hz) of the frontal and central electrodes, and the theta/beta and theta/alpha ratios in motor cortices will be analyzed by the SPSS software version 24.

#### Dietary intake and physical activity assessment

To evaluate dietary intake of subjects, a 3-day (1 weekend day and 2 nonconsecutive weekdays) food recall will be used at weeks 0, 4, and 8. The short form of International Physical Activity Questionnaire (IPAQ) [52] will be used for assessment of physical activity at weeks 0, 4, and 8.

#### Anthropometric evaluations

Height will be measured in standing position at weeks 0 and 8, using a non-stretched tape with an accuracy of 0.5 cm. Weight will be measured based on standard protocols with light clothes and without shoes by seca scale with an accuracy of 100 g. Body mass index (BMI) will be calculated by the following formula: weight (kg)/height squared (m^2^).

#### Laboratory assessments

Laboratory assessments will be performed at weeks 0, and 8. 5 cc blood will be drawn after 12 h fasting and will be centrifuged for 10 min at a speed of 3600 rpm. Serum samples poured into the microtubes will be immediately frozen at − 80 ° C. NO, MDA, and hs-CRP will be measured by ELISA method using Q-1-DiaPlus, USA, kits. In addition, using chemiluminescent microparticle immunoassay (CMIA) method, measuring the serum concentration of vitamin D will be performed. Serum calcium and phosphate will be measured by Biosystems, Barcelona, Spain, kits using colorimetric analysis method. Measurements will be performed based on standard methods.

#### Data management

Data will be entered electronically at the participating site. In addition, the forms will be kept on file at the participating site. Personnel at the participating site will send the copy of forms (files) to data coordinating center (DCC). The DCC will send weekly email reports about missing data, missing forms, and missing visits. Personnel at the participating site will review these reports for accuracy. The DCC will monitor source documents and will conduct at least one on-site monitoring visit during the study. DCC's primary objectives during site visits are to educate, support, and resolve problems. This process will be independent from investigators. Participant files will be maintained for a period of 2 years after completion of the trial.

#### Safety and adverse effects

Any possible adverse event will be reported to the Ethical Committee of Shahid Sadoughi University of Medical Sciences and Health Services (Fig. 2). Based on the type and severity of adverse event relate to supplementation, the ethical committee will make a decision on removing the participant or giving an exclusive code or etc. In addition, to evaluate possible toxicity and hypervitaminosis after supplementation with vitamin D, serum level of calcium will be measured at the beginning of the study and after intervention [53].

**Fig. 2 Fig2:**
[figure not shown]
Schedule for enrollment, intervention, and assessment. CPRS, Conners parent rating scale; EEG, electroencephalography; hs-CRP, high-sensitivity C-reactive protein; IPAQ, international physical activity questionnaire; MDA, malondialdehyde; NO, nitric oxide

#### Monitoring data, data accessibility, and confidentially

This RCT will be supervised by a Data Monitoring Committee (DMC). The principal investigator will have access to the final data of the study, and such access for other investigators is limited. There is no plan for granting public access to the full protocol, participant-level dataset, and statistical code. We will present the findings of this study only through the publication. To maintain participant confidentiality, all laboratory samples, reports, data collection, process, and administrative forms will be identified by a coded ID number. All information of participants will be stored securely in locked room with limited access at the study site.

#### Statistical analysis

SPSS version 24 (SPSS, Inc.) will be used for data analysis. The analyses will be performed using the intention-to-treat (ITT) approaches. Using Kolmogorov-Smirnov test, normal distribution of variables will be assessed. Comparing the qualitative variables between two groups will be performed using chi-squared test. To compare the means of normal variables at baseline, at the end of study, and compare the mean changes of normal data between two groups, independent *t*-test will be used. To compare normal variables within the groups, paired sample *t*-test will be applied. Using Mann-Whitney *U* test, comparing abnormal data between the two groups at baseline and after the intervention as well as comparing the mean changes of abnormal data between two groups will be performed. Wilcoxon test will be used to compare the abnormal data within the groups. To control covariates, ANCOVA will be carried out. *P* < 0.05 will be considered significant.

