### Objectives

Primary objectives are as follows:Compare the status of brain waves between the 2 groups and within each group, before and after intervention.Compare the mean ADHD symptoms severity between the 2 groups and within each group, before and after intervention.

In addition, the following objectives are the secondary objectives of the study:Compare the mean serum hs-CRP between the 2 groups and within each group, before and after intervention.Compare the mean of serum MDA, between the 2 groups and within each group, before and after intervention.Compare the mean of serum NO, between the 2 groups and within each group, before and after intervention.

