### Randomization and blinding

Simple (unrestricted) randomization will be performed, and participants will be divided randomly into two groups including intervention (vitamin D, *n* = 25) and control (placebo, *n* = 25) by a person who is not involved in the trial using the computer-generated random number table (produced by random allocation software) [50]. Concealing allocation sequence from those assigning participants to the intervention groups will be performed utilizing opaque sealed envelopes. Boxes of vitamin D or placebo will be named as A and B by a third person that is not involved in the study. Participants, investigators, and laboratory staff will be blinded to the treatment allocation. Randomization codes will be unlocked only after all patients complete the study protocol.

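### The randomised arms are significance-tested at baseline, which tells the reader nothing useful, while the stated between-group outcome tests leave the baseline value out as a fixed covariate

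*Protocol article*

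**What the plan says.** All references are to the protocol article.

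- **Statistical analysis.** The independent t-test is used "To compare the means of normal variables at baseline, at the end of study", and also for the mean changes between the two groups. The Mann-Whitney test is used for "comparing abnormal data between the two groups at baseline and after the intervention" and for changes. One two-group threshold of 0.05 covers all tests. ANCOVA gets a single sentence: "To control covariates, ANCOVA will be carried out". The section does not say which covariates are meant, or whether ANCOVA or the simple tests carry the conclusion.
- **Objectives.** The two primary objectives read "Compare the status of brain waves between the 2 groups and within each group, before and after intervention" and "Compare the mean ADHD symptoms severity between the 2 groups and within each group, before and after intervention". The secondary objectives follow the same pattern for hs-CRP, MDA and NO.
- **Randomization and blinding.** "Simple (unrestricted) randomization will be performed", with 25 children per arm. No stratification is described.

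**The concern.** Randomisation makes the null hypothesis of a baseline test true for the set as randomised. A significant result there is a chance finding, and a non-significant one does not show that the arms are alike. With 50 children and unrestricted randomisation, sizeable chance differences in a prognostic variable are quite likely, and the test misses most of them.

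What matters for the conclusion is how the outcome comparison handles the baseline value. The comparisons the article spells out are the end-of-study difference, which ignores baseline, and the difference in change, which subtracts it in full. Neither uses it efficiently unless the correlation between baseline and week 8 happens to be near 0 or near 1. At stake are power in a small trial and the reliability of the result when the arms start out unequal.

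**Working it through.** **Inputs from the article.** 25 per arm; two groups; threshold 0.05 (taken as two-sided); drop-out about 10%, so 25 × 0.9 = 22.5, taken as 22 analysed per arm.

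**Assumptions, not in the article.** Correlation r between baseline and week 8 of 0.5 to 0.7. Equal SDs, normal data. A true effect of 0.835 SD, which is what the article's sample-size formula returns for 22.5 per arm: 2 × (1.96 + 0.8416)² / 0.835² = 22.5. The article gives no means or SDs, so its 25 per group cannot be recomputed from its own inputs. Working backwards, 0.85 to 0.86 SD gives 22 per arm and then 25 after drop-out, so the figure is possible.

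**Step 1: what the baseline test can flag.** The smallest significant observed difference is t(0.975, 2n−2) × √(2/n).
- n = 25: 2.011 × √(2/25) = 0.57 SD.
- n = 22: 2.018 × √(2/22) = 0.61 SD.

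An observed difference of 0.5 SD gives P = 0.083 (n = 25) or 0.105 (n = 22). By chance alone, at 25 per arm, differences above 0.3 SD arise in about 29% of randomisations and above 0.5 SD in about 8%.

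**Step 2: effect of an unflagged imbalance.** Take an imbalance D = 0.5 SD, n = 25, r = 0.5. The week-8 difference is shifted by r × D = 0.25 SD. Its standard error is √(2/25) = 0.283, so the critical value is 1.96 × 0.283 = 0.554. Its SD given the imbalance is 0.283 × √(1 − 0.25) = 0.245. The chance of rejecting a true null is about 1 − Φ((0.554 − 0.25)/0.245) = 11%. The change score is shifted by (r − 1) × D = −0.25 SD, also giving 11%. At r = 0.7 the two figures are 16% and 8.5%.

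**Step 3: power at 22 per arm.** The noncentrality is (0.835/k) × √(22/2), with k = 1 for the week-8 test, √(2(1 − r)) for the change score and √(1 − r²) for ANCOVA. For the week-8 test this is 0.835 × 3.317 = 2.77, giving 77%. Simulation agrees for all three; the ANCOVA column is the simulated value, which allows for estimating the slope.

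| r | Week-8 test | Change score | ANCOVA on baseline |
|---|---|---|---|
| 0.5 | 77% | 77% | 87% |
| 0.6 | 77% | 86% | 92% |
| 0.7 | 77% | 94% | 96% |

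**Step 4: false positives (simulated, 22 per arm, no true effect).** Across all trials, each of the three tests rejects about 5% of the time. About 13% of trials have a baseline imbalance above 0.4 SD with P ≥ 0.05. In that subset the week-8 test rejects about 9 to 12% of the time for r = 0.5 to 0.7, the change score about 7 to 9%, and ANCOVA about 5%.

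**The case against.** Four points deserve weight.

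- **The covariate list may be elsewhere.** The article condenses a fuller protocol, and a list of ANCOVA covariates is commonly left to that or to an analysis plan. This stands: the absence of a list is not the point. The point is what the article does state, namely baseline tests and unadjusted outcome comparisons, with ANCOVA added in a role it does not define.
- **Covariates picked by baseline P values.** A reader might infer that the baseline tests exist to choose the covariates, or that P ≥ 0.05 will be read as balance. The article says neither, so this is a risk only. Nor does it follow that type I error would be inflated overall: adjusting only after a significant baseline test gives an overall rate of about 0.03 to 0.045, which is conservative. The raised rates in Steps 2 and 4 apply to trials with an imbalance, not to trials in general.
- **The change score is planned too.** Baseline is therefore not wholly ignored. This stands and narrows the gain: ANCOVA is about 10 points better than the change score at r = 0.5, but only about 6 at r = 0.6 and 2 to 3 at r = 0.7.
- **Two limits on the reading of the text.** In the Objectives, the words about before and after may belong mainly to the within-group comparison; only the Statistical analysis section is unambiguous. And the Adherence section removes the data of children who take under 80% of capsules. If baseline is tested in that reduced set, randomisation no longer guarantees the null, so it would be too strong to call every significant baseline result a false positive. That is still no reason to report baseline P values.

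**Conclusion.** The point holds in a limited form. Baseline tests between the arms are plainly planned and are uninformative for the set as randomised. On their own they change no outcome test. The practical loss is that the stated between-group comparisons do not fix the baseline value as a covariate. Under the assumed effect, arm size and correlations, that costs about 10 to 19 points of power against the week-8 test (87 − 77 and 96 − 77) and about 2 to 10 against the change score. It also leaves a conditional false-positive rate above 5% in roughly one trial in eight. The power figures depend on values the article does not give; the 0.57 SD threshold depends only on the stated arm size and alpha.

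**What to change.** 1. In Statistical analysis, delete the between-arm tests at baseline. Describe baseline by arm with mean (SD), median (quartiles) or n (%), without P values.
2. In Objectives, reword each item so that the between-group comparison is made after intervention only.
3. State that the primary between-group analysis of every continuous outcome is ANCOVA of the week-8 value, adjusted for that outcome's own baseline value. The end-of-study and change-score tests can stay as supportive analyses.
4. State that no covariate will be chosen from baseline P values. Adding age and sex as fixed covariates is optional.

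The cost is a few changes of wording. The baseline value of each outcome is already to be collected, no participants are added, and the number of tests falls.

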### Sample size

Sample size is calculated based on means and standard deviations for Conners’ ADHD Index, as the primary outcome of the study of Gow et al. [49] by considering 95% confidence interval, 80% power (*α* = 0.05 and *β* = 0.2), and using the following formula:$$n=\frac{{\left(\textrm{z}\frac{\alpha }{2}+\textrm{z}\upbeta \right)}^2\times 2{S}^2\ }{{\left(x1-x2\right)}^2}$$

Considering a drop-out rate of approximately 10%, the final sample size needed was estimated to be 25 per group. All participants will be included in the RCT if they meet the inclusion criteria and are willing to participate in the study, until the estimated sample size is completed.

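### Each continuous outcome gets competing between-arm tests at 0.05 with none named as deciding; one pre-named baseline-adjusted ANCOVA would remove the choice and usually gain precision

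*Protocol article*

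**What the plan says.** The Statistical analysis section of the protocol article first applies a Kolmogorov-Smirnov test to each variable. Variables judged normal are compared between arms by independent t-test at baseline, and then twice more: "at the end of study, and compare the mean changes of normal data between two groups". Variables judged non-normal follow a parallel Mann-Whitney route, "comparing abnormal data between the two groups at baseline and after the intervention", and again on changes. One further sentence follows: "To control covariates, ANCOVA will be carried out". It names neither the outcomes nor the covariates, and does not say how this result ranks against the others. A single threshold covers everything: P "< 0.05 will be considered significant".

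The Objectives section does not settle the matter. It asks for comparisons between and within groups, before and after treatment, without choosing the final value or the change.

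The Sample size section uses the formula for an unadjusted comparison of two means, "by considering 95% confidence interval, 80% power", and reports that "the final sample size needed was estimated to be 25 per group". It prints no means, standard deviation or target difference.

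**The concern.** The week-8 test, the change test and a baseline-adjusted ANCOVA all address the same question, but they correct differently for chance baseline imbalance. Let Dy be the between-arm difference at week 8 and Dx the difference at baseline. The week-8 test uses Dy, the change test uses Dy − Dx, and ANCOVA on baseline uses Dy − b·Dx with b estimated from the data. With simple randomisation and about 25 children per arm, Dx will often be far enough from zero for the three P-values to fall on different sides of 0.05. The plan does not say which one then decides, so a favourable result can be picked without departing from the text.

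Precision is also at stake. The outcomes are measured before treatment, but the week-8 test ignores that value and the change test subtracts it in full. In a trial this small, either can waste information already paid for.

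**Working it through.** **Inputs.** Two-sided alpha 0.05, power 80%, about 10% dropout and 25 per group come from the Sample size section. The baseline to week-8 correlation r is not given. It is an assumption, varied from 0 to 0.7. Equal variance at both times is also assumed.

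**Effect size implied by the plan.** The stated 25 cannot be derived forward, because the means and SD are not printed. Working backward, 22 / 0.9 = 24.4, which rounds up to 25. By the same step 21 gives 24 and 23 gives 26, so 22 evaluable per arm is the figure consistent with the plan. Inverting the plan's formula:

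d = √[2 × (1.960 + 0.842)² / 22] = √(2 × 7.849 / 22) = 0.845.

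This d is a back-calculation, not a figure in the document.

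**Variance of the arm difference, relative to the week-8 test (large samples).**

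- Week-8 test: 1
- Change test: 2(1 − r)
- ANCOVA on baseline: 1 − r²

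ANCOVA against change is (1 − r²) / [2(1 − r)] = (1 + r)/2, which is below 1 for every r < 1. Estimating the slope multiplies the ANCOVA variance by about 1 + 1/(2n − 4) = 1 + 1/40 = 1.025 at n = 22. ANCOVA therefore beats the week-8 test only when (1 − r²) × 1.025 < 1, that is, r above about 0.16. The same factor leaves it ahead of the change test up to r of about 0.95.

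**Type I error.** Simulation under no effect, bivariate normal data, 22 per arm, 40,000 trials per row. Each single test rejected in about 5%.

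| r | week-8 or change significant | any of the three significant |
|---|---|---|
| 0 | 8.4% | 8.7% |
| 0.2 | 8.7% | 9.0% |
| 0.3 | 9.1% | 9.4% |
| 0.5 | 9.1% | 9.6% |
| 0.7 | 9.3% | 10.0% |

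With 25 per arm, the any-of-three rate over the same range of r was 8.6 to 10.1%. Three independent tests would give 1 − 0.95³ = 14.3%. The actual rate is lower because the tests are correlated.

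**Power.** Simulation, 22 per arm, d = 0.845.

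| r | week-8 | change | ANCOVA | ANCOVA minus week-8 (points) |
|---|---|---|---|---|
| 0 | 78.2% | 49.2% | 77.2% | −1.0 |
| 0.1 | 78.7% | 53.4% | 78.0% | −0.7 |
| 0.2 | 78.5% | 58.0% | 79.2% | +0.7 |
| 0.3 | 77.9% | 63.4% | 80.6% | +2.7 |
| 0.5 | 78.2% | 78.3% | 87.7% | +9.4 |
| 0.7 | 77.7% | 94.2% | 96.4% | +18.7 |

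The week-8 figure is about 78% and not 80% because the plan's formula uses the normal distribution and the test uses t.

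**Normality pre-test.** With the Kolmogorov-Smirnov switch built in (6,000 trials per setting, normal or lognormal data, r = 0.3 to 0.7), each t-or-Mann-Whitney comparison rejected in 4.4 to 5.5% under no effect. The any-of-three rate was 9.6 to 10.8%.

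**The case against.** *The ANCOVA may be only a secondary adjusted analysis.* Its sentence names no outcome or covariate, and the sample size rests on an unadjusted comparison. Reading it as a third test of every outcome is an inference, and naming covariates is often left to an analysis plan. That is fair. But the article itself prescribes both the week-8 and the change comparison, unranked, and those two alone give 8.4 to 9.3%. The conflict is in what the text fixes, not in what it leaves out.

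*The power gain is not guaranteed.* This stands. Neither r nor the effect size is in the document. For the EEG outcome, r may be low because children enter on abnormal theta and beta findings. If, for illustration, only the upper half of baseline values were enrolled, an r of 0.5 would fall to about 0.33 and 0.7 to about 0.51. A reader might infer that ANCOVA always adds power at no price. Against the week-8 test, it does not when r is below about 0.15 to 0.2.

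*The normality pre-test is the culprit.* A reader might infer this too, but the simulations do not support it: the switch alone leaves error near 5%. What can be said is narrower. Mann-Whitney does not compare mean changes, and it uses the baseline only by full subtraction.

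*The trial's error rate is 10%.* The document does not say that any significant result will count. The figure is what the text permits, not what it commits to.

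**Conclusion.** The concern holds in a limited form. The article sets at least two, and on its natural reading three, between-arm tests of the same continuous outcome at 0.05, and none decides. If any may count, the error for one outcome is about 8.5 to 10%, against about 5% for one pre-named ANCOVA. This result changes little over r from 0 to 0.7.

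The precision argument is conditional. In the simulations ANCOVA beats the change test at every r tried. Over the week-8 test it gains nothing near r = 0.1, about 3 points at 0.3, 9 at 0.5 and 19 at 0.7, assuming d = 0.845 and 22 evaluable per arm. Settling this does not control error across the two primary outcomes or the several EEG measures.

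**What to change.** Before the allocation codes are opened, record in a dated amendment:

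- One deciding analysis for each continuous outcome: ANCOVA of the week-8 value on arm and the baseline value of that outcome, reported as an adjusted difference with 95% confidence interval.
- Any further covariates as a pre-listed set of baseline variables only. Diet, activity or BMI measured after randomisation should not enter.
- The scale of each outcome, fixed in advance (for example, log hs-CRP). It should not depend on a normality test or a check for skewness in the trial data, since that would bring back a data-driven choice.
- The t-tests and Mann-Whitney tests as sensitivity analyses.

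No extra children, visits or software are needed. The real cost is timing. Recruitment was expected to end on 30 August 2021, treatment lasts 8 weeks, and the article appeared in October 2022. If that schedule held, follow-up was complete before publication, so the choice is credible only if documented while the codes are still locked. If they are already open, the report should say so and show all the comparisons together.
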